**A randomised trial to assess the effectiveness of different primaquine regimens for the radical treatment of vivax malaria in Kolkota**

| Principal Investigator: | [name] |
| --- | --- |
| Sponsor | Faculty of Tropical Medicine, Mahidol University |
| Funder | Wellcome Trust |

**Protocol development team:** [name], Prof [name], Prof [name], [name], Dr [name]

Confidentiality Statement

This document contains confidential information that must not be disclosed to anyone other than the Sponsor, the Investigator Team, host institution, relevant ethics committee and regulatory authorities.

List of abbreviations

CRF Case record form

DSMB Data and Safety Monitoring Board

G6PD Glucose-6-phosphate dehydrogenase

GCP Good Clinical Practice

Hct Haematocrit

PCR Polymerase Chain Reaction

PCT Parasite Clearance Time

SAE Serious Adverse Event

SYNOPSIS

| Study Title | A randomised trial to assess the effectiveness of different primaquine regimens for the radical treatment of vivax malaria in Kolkota |
| --- | --- |
| Trial Design | Open-label randomised trial to assess the relapse rates of *P. vivax* malaria in patients in Kolkota with two different primaquine regimens. |
| Trial Participants | Patients with acute uncomplicated *P. vivax* malaria |
| Sample size | 50 patients per drug arm. Estimated total sample size 150. |
| Inclusion Criteria | - Male or female, aged from 3 years to 65 years old, inclusive - Acute uncomplicated *P. vivax* malaria, confirmed by positive blood smear - Fever defined as > 37.5°C tympanic or oral temperature or a history of fever within the last 24 hours - Written informed consent (by legally acceptable representative in case of children) - Willingness and ability of the patients/guardians to comply with the study protocol for the duration of the study |
| Exclusion Criteria | - Signs of severe/complicated malaria (WHO, 2000) - Haematocrit < 25% or Hb < 8 g/dL at enrollment - Acute illness other than malaria requiring treatment - For females: pregnancy, breast feeding - Patients who have received chloroquine within the previous 7 days - History of allergy or known contraindication to trial drugs. - Severe G6PD deficiency |
| Planned Trial Period | 24 to 30 months (January2003 – June 2005) |
| Primary Objective | To compare the effectiveness of primaquine 0.25mg base/kg/day given for 5 days versus 14 days with a standard chloroquine regimen in *P*. vivax malaria. |
| Secondary Objectives | - To measure the clinical and parasitological responses with chloroquine alone and two chloroquine –primaquine regimens. - To assess safety and tolerability |
| Primary endpoint | Recurrence rates over 12-15 months follow-up. |
| Secondary endpoints | - Parasite clearance time assessed by microscopy - Fever clearance time (i.e. the time taken for the tympanic temperature to fall below 37˚C and remain there for at least 24 hours) - Genotype assessments |

BACKGROUND AND RATIONALE

*Plasmodium vivax* malaria is notoriously difficult to eliminate, largely because of relapses which are derived from activation of liver hypnozoites. The only effective radical treatments for *P.vivax* infections are 8-aminoquinoline antimalarials, all of which produce oxidant haemolyis. These drugs are potentially dangerous in areas where glucose 6 phosphate dehydrogenase deficiency (G6PD) is common (i.e. most tropical countries). Primaquine is widely recommended, but often not prescribed. The proportion of vivax infections which relapse varies considerably across the tropical world. India has most of the world’s *Plasmodium vivax* malaria (1). There have been few prospective studies of relapse patterns in India (2-5). More recent investigations indicated low relapse rates, which was one reason why India adopted a five day primaquine regimen for radical treatment of vivax malaria over the past half-century (6, 7). But relapse rates can be underestimated if follow-up terminates before relapses emerge. Long latency *P.vivax* was prevalent over Europe, and much of Asia. In the temperate areas relapses usually occurred 7 to 10 months after the initial febrile illness. Further north there was usually no primary illness, and symptoms occurred 7-10 months after sporozoite inoculation. Although generally thought to be confined to temperate regions such as the Koreas, long latency *P.vivax* is likely be much more widespread throughout the tropics. It is certainly also prevalent in Central America, North Africa, the horn of Africa, the middle East, Afghanistan, Central Asia, the Indian sub-continent (3) and China. Clear evidence for long latency in Indian *P.vivax* was documented in the first half of the twentieth century (8), and is supported by more recent studies (3). In order to assess the effectiveness of short course primaquine regimens, and to determine whether long latency *P.vivax* was present around Kolkata, a prospective comparative trial supported by parasite genotyping was conducted with up to 450 days follow-up.

**OBJECTIVES**

*Primary Objective*

To compare the effectiveness of primaquine 0.25mg base/kg/day given for 5 days versus 14 days together with a standard chloroquine regimen in *P*. vivax malaria.

*Secondary Objectives*

To measure the clinical and parasitological responses with chloroquine alone and two chloroquine –primaquine regimens.

To assess safety and tolerability of the different regimens

**TRIAL DESIGN**

Study sites

*Summary of Trial Design*

This will be a prospective open label comparison of chloroquine (CQ) alone versus CQ plus 5 days unobserved primaquine or CQ plus 14 days unobserved primaquine in patients with acute vivax malaria in Kolkota. Patients will be followed for 15 months and primary and recurrent infections were genotyped.

Study duration; **2 years**

*Primary and Secondary Endpoints*

Primary Endpoint

Recurrence rate of vivax malaria over 15 months

Secondary Endpoints

Parasite clearance time assessed by microscopy

Fever clearance time (i.e. the time taken for the tympanic temperature to fall below 37˚C and remain there for at least 24 hours)

Genotype assessments Parasite clearance time assessed by microscopy

*Trial Participants*

Overall Description of Trial Participants

Male and non-pregnant female patients aged between 36 months and 65 years with acute uncomplicated vivax malaria are the target study population. All study patients must meet the applicable inclusion and exclusion criteria.

I*nclusion Criteria*

- Male or female, aged from 36 months to 65 years old, inclusive
- Acute uncomplicated *P. vivax* malaria, confirmed by positive blood smear with asexual forms of *P. vivax*
- Fever defined as > 37.5°C tympanic temperature or a history of fever within the last 24 hours
- Written informed consent (by legally acceptable representative in case of children)
- Willingness and ability of the patients/guardians to comply with the study protocol for the duration of the study

*Exclusion Criteria*

- Signs of severe/complicated malaria (WHO, 2000)
- Haematocrit < 25% or haemoglobin (Hb) < 8 g/dL at enrollment
- Acute illness other than malaria requiring treatment
- For females: pregnancy, breast feeding
- Patients who have received antiamalrial treatment within the previous 7 days
- History of allergy or known contraindication to study drugs
- G6PD deficiency;patients who are deficient on spot testing will not be allocated to the two primaquine groups.

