Subjects who fulfil all the inclusion criteria and have none of the exclusion criteria will be randomised 1:1;1 to one of the three treatment arms. Allocation will be done by drawing the next sequential numbered opaque envelope, which contains the study number of the patient referring to the study treatment. The subjects will be assigned a study arm through a computer-generated randomisation scheduleThis is an open-label study so the blinding of investigators and patients is not applicable. However, the randomisation procedure allows for adequate drug allocation concealment before envelopes are opened. All laboratory investigations will be performed without knowledge of the treatment allocation.

*Blood sampling*

On admission

On study admission, immediately before drug administration, blood will be collected for the following:

- parasite count
- EDTA 2mL whole blood sample for PCR parasite genotyping
- haematocrit

G6PD spot test

*Study drug regimens*

(1) chloroquine (25mg base /kg total) only

(2) chloroquine (25mg base /kg total) followed by primaquine 0.25mg base/kg/ day for five days

(3) chloroquine (25mg base/kg total) followed by primaquine 0.25mg base/kg/ day for 14 days

*For recurrences:*

chloroquine (25mg base /kg total) followed by primaquine 0.25mg base/kg daily for 21 days.

The first dose will be observed but all subsequent antimalarial doses will be taken at home. Each patient will be instructed on the need to complete the full course of treatment.

*Follow up procedures*

Patients will be seen daily until a febrile then weekly for one month and thereafter every one to two months for 15 months. If vivax malaria recurs blood will be taken for parasite genotyping and comparison with the original infection.

*Additional visits*

Patients presenting to the clinic with a fever or other symptoms on unscheduled days will be assessed by the study physician. Their temperature will be recorded and blood smear will be made for any patient with a documented fever (oral or tympanic temperature ≥ 37.5˚C) or a history of fever. Patients will be treated as clinically indicated.

Patients with recurrent parasitaemia

Patients with a recurrent parasitaemia during follow up will have blood taken for the following:

- parasite speciation and count
- haematocrit
- if parasitaemic: EDTA 2mL whole blood sample for PCR parasite genotyping

*Discontinuation/ Withdrawal of Participants from the Study*

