**STATISTICAL considerations**

Sample size justification

The sample size was calculated based on an assumption that relapse rates would be 30% in the chloroquine only group and 4% in the 14 day primaquine group.

To allow for 20% loss to follow up or incomplete data, a total of 50 patients per arm will be recruited to detect such a difference with 95% confidence and 80% power. The groups will be compasred by survival analysis..

Statistical Analyses

Proportional data

These will be compared using chi squared or Fisher’s exact test, as appropriate. Crude proportions will be calculated with the exact 95% confidence intervals (CI), where relevant.

Continuous data

These will be summarised by medians (IQR, ranges) and means (standard deviations, 95% CIs), as appropriate, and will include the parasite counts and laboratory parameters. Comparisons of continuous data will be assessed using the paired/unpaired t tests or the sign rank/Mann Whitney U tests, as appropriate.

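### The G6PD eligibility rule contradicts itself and can be read as admitting deficient patients to the chloroquine-only arm alone, which would make the chloroquine contrasts partly non-randomised

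*Protocol*

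**What the plan says.** Three places in the protocol bear on this, with two supporting details.

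- Synopsis, Exclusion Criteria: the only G6PD entry is "Severe G6PD deficiency". The term severe is not defined.
- TRIAL DESIGN, Exclusion Criteria: "G6PD deficiency;patients who are deficient on spot testing will not be allocated to the two primaquine groups".
- Procedures, Randomisation and blinding: patients who meet every inclusion criterion and who "have none of the exclusion criteria will be randomised 1:1;1 to one of the three treatment arms". The mechanism is a single sequence: "Allocation will be done by drawing the next sequential numbered opaque envelope". No separate list, stratum or cohort for deficient patients is described.

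The G6PD spot test appears under Screening blood & urine tests. It appears again under Blood sampling, in the list introduced by "On study admission, immediately before drug administration, blood will be collected for the following".

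The sample size rests on a contrast that uses the chloroquine arm: it assumes that "relapse rates would be 30% in the chloroquine only group and 4% in the 14 day primaquine group". The primary objective compares 5 days with 14 days of primaquine.

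**The concern.** Take a patient who is deficient on the spot test, but not severely. Under the synopsis the patient is eligible and can be randomised to any arm. Under the body the patient either is excluded or may go only to chloroquine alone, depending on how the line is read. The protocol does not settle which.

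If the line is applied as an allocation restriction, a deficient patient receives chloroquine alone with probability 1, against 1/3 for everyone else. G6PD status would then differ between the chloroquine arm and both primaquine arms by design. Chloroquine versus either primaquine regimen would mix randomised patients with patients placed by phenotype. A later analysis plan could leave such patients out of a comparison, but it could not make their allocation random. Eligibility and allocation therefore have to be settled in the protocol.

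**Working it through.** **1. The plan's own figure.** Inputs from Sample size justification: 30% versus 4%, 95% confidence, 80% power, 20% loss, 50 per arm. Sidedness is not stated; two-sided 5% is assumed.

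Without continuity correction, with mean proportion 0.17:

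n = [1.96 × √(2 × 0.17 × 0.83) + 0.8416 × √(0.30 × 0.70 + 0.04 × 0.96)]² / 0.26² = 31.6, so 32 per arm.

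With continuity correction:

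n = (31.6/4) × [1 + √(1 + 4/(31.6 × 0.26))]² = 38.9, so 39 per arm.

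Allowing for loss: 39/0.80 = 48.75, so 49. This agrees with the stated 50, and the fix below does not disturb it.

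**2. Share of the chloroquine arm.** The protocol gives no prevalence of deficiency, so g, the share of enrolled patients who are deficient, is an assumption. The calculation takes 150 enrolled, all deficient patients on chloroquine alone and the rest split 1:1:1.

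Share = 150g / [150(1 − g)/3 + 150g] = 3g/(1 + 2g).

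| Assumed g | Deficient patients | Each primaquine arm | Chloroquine arm | Deficient share of chloroquine arm |
|---|---|---|---|---|
| 3% | 4.5 | 48.5 | 53 | 4.5/53 = 8.5% |
| 5% | 7.5 | 47.5 | 55 | 7.5/55 = 13.6% |
| 10% | 15 | 45 | 60 | 15/60 = 25.0% |

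Over a wider assumed range of 2% to 20%, the share runs from 5.8% to 42.9%. In every case it is 0% in each primaquine arm.

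**3. Possible effect on recurrence.** Shift in the chloroquine rate = share × (risk in deficient patients − 30%). With equal risk the shift is zero. If the risk in deficient patients were 15% or 45% (assumed, since the protocol is silent), the shift would be:

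- 3%: 0.085 × 15 = 1.3 points either way
- 5%: 0.136 × 15 = 2.0 points either way
- 10%: 0.25 × 15 = 3.75 points either way

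The planned difference is 30 − 4 = 26 points.

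**4. Possible effect on power.** Suppose deficient patients count towards the chloroquine quota but are removed from the comparison. Evaluable randomised chloroquine patients then fall from 50 × 0.80 = 40 to 40 × (1 − 0.136) = 34.5 at 5%, or 40 × (1 − 0.25) = 30 at 10%. Power against 40 patients on 14-day primaquine falls from 88.7% to 86.6% or 84.4% (normal approximation, no continuity correction). Comparability is at stake far more than power.

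**The case against.** The strongest reply is that the protocol, read strictly, already excludes every deficient patient. G6PD deficiency stands under Exclusion Criteria, and only those who "have none of the exclusion criteria will be randomised 1:1;1 to one of the three treatment arms". On that chain no deficient patient is ever randomised, and the clause about the primaquine groups merely explains the reason. The regimen for recurrences contains primaquine and makes no exception for G6PD status, which also fits a trial without deficient patients. The spot test is listed at screening, so its result could be known in time.

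Much of this stands, and it rules out several stronger readings that a reader might infer:

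- *That the plan intends a non-randomised chloroquine group.* Nothing says that deficient patients receive chloroquine alone, count towards the 150 or enter a comparison. The wording permits this; it does not direct it.
- *That everyone enrolled is randomised whatever their G6PD status.* The randomisation text is conditional on having no exclusion criterion, so it is not a third, competing G6PD rule.
- *That primaquine envelopes would be overridden or skipped.* No such procedure is described, and a patient known at screening to be deficient need not draw an envelope.
- *That recurrence results would be biased.* The figures show an imbalance in composition. The protocol links G6PD deficiency to haemolysis under treatment, not to relapse.

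The strict reading still does not close the matter. If all deficient patients were excluded, a clause barring them from two named arms would have no work to do. The synopsis would also still disagree, since it excludes severe deficiency only.

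**Conclusion.** The contradiction is real: the synopsis and the body state different G6PD rules, and the body's line can be read either as exclusion from the trial or as restriction to chloroquine alone.

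The consequence is conditional. Only under the restriction reading would the chloroquine contrasts, including the 30% versus 4% contrast behind the sample size, become partly non-randomised. About 8%, 14% or 25% of the chloroquine arm would be affected at an assumed prevalence of 3%, 5% or 10%. These figures also assume that every deficient patient is enrolled; if severe cases were kept out, as the synopsis says, the numbers would be lower.

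A reader might infer that the primary comparison is compromised. It is not: deficient patients would be barred from both primaquine arms, so 5 days versus 14 days keeps its randomised basis. With the total fixed at 150, those two arms would only be slightly smaller than 50.

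**What to change.** - State one G6PD definition in the synopsis and in the Exclusion Criteria under TRIAL DESIGN. Which definition is for the clinical team to decide.
- In Randomisation and blinding, state that only patients eligible for all three arms are randomised, and that the screening spot-test result is known before an envelope is drawn. Clarify what the second listing of the test at admission is for.
- If deficient patients are to be followed on chloroquine alone, register them as a separate non-randomised cohort, outside the 150 and outside every between-arm comparison.
- If deficient patients are enrolled in any form, reconcile the regimen for recurrences, which makes no reference to G6PD status, with the G6PD line in the Exclusion Criteria. No clinical rule is proposed here.

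The cost is wording in the eligibility and randomisation sections, a few screened patients lost from the randomised set, and slightly longer recruitment. The planned 50 per arm stands unchanged.

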***Procedures***

*Informed Consent*

The subject (or witness if illiterate) or the parent or guardian of a minor must personally sign and date the latest approved version of the informed consent form before any study specific procedures are performed. Written and verbal versions of the participant information and informed consent in the local language will be presented to the participants detailing no less than: the exact nature of the study; the implications and constraints of the protocol; the known side effects and any risks involved in taking part. It will be clearly stated that participation is voluntary and that the participant or guardian is free to withdraw from the study at any time for any reason without prejudice to future care, and with no obligation to give the reason for withdrawal.

Written informed consent will be obtained by means of participant or guardian dated signature or thumb print (if unable to write) and dated signature of the person who presented and obtained the informed consent.

*Screening, Eligibility and Baseline Assessments*

Patients who present at the participating sites will be screened to assess eligibility. Full consent/assent will be obtained before any enrolment procedures are conducted. It will be made clear from the outset that refusal to participate will not jeopardize subsequent antimalarial treatment.

*Demographics and Medical History*

Basic demographic and epidemiological data (e.g. sex, age, address, prior treatment and a full medical history) will be recorded by the study staff.

*Physical Examination and Vital Signs*

Physical examination will be conducted by a qualified investigator. Weight, pulse, blood pressure, respiratory rate, temperature, spleen and liver size will be recorded.

*Drug history*

All prescribed or over-the-counter and traditional medications used within the last 7 days will be recorded. Any drug allergies will be recorded.

*Screening blood & urine tests*

- A parasite count from Giemsa stained thick and thin blood films
- Full blood count or haematocrit
- G6PD spot test

*Randomisation and blinding*

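### The protocol states G6PD eligibility inconsistently, and the 21-day primaquine rule for recurrences carries no G6PD exception

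*Protocol*

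**What the plan says.** Four places in the protocol bear on this point.

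- **Synopsis, Exclusion Criteria:** the entry is "Severe G6PD deficiency". No cut-off for severity is given.
- **Trial Design, Exclusion Criteria:** the entry is "G6PD deficiency;patients who are deficient on spot testing will not be allocated to the two primaquine groups". A separate bullet excludes "History of allergy or known contraindication to study drugs".
- **Procedures, Randomisation and blinding:** "Subjects who fulfil all the inclusion criteria and have none of the exclusion criteria will be randomised", in a 1:1:1 ratio to the three arms, by drawing the next numbered envelope. No restricted or separate allocation is described.
- **Procedures, Study drug regimens:** every recurrence is to be treated with chloroquine "followed by primaquine 0.25mg base/kg daily for 21 days". No condition on G6PD status is attached. Only the first dose is observed.

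The only G6PD measurement listed is the "G6PD spot test". Background and Rationale says that 8-aminoquinolines all cause oxidant haemolysis and may be dangerous where G6PD deficiency is common.

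**The concern.** G6PD status is the one eligibility criterion tied to a hazard that the protocol itself names for its study drug, so it needs a single meaning. As written, a patient with mild deficiency can be classed as eligible for any arm, for chloroquine alone, or for none, depending on which sentence the site follows.

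Two things are at stake if deficient patients enter on chloroquine alone. First, they reach that arm by their test result and not by the envelope. The chloroquine arm then contains a type of patient that the 14-day arm cannot contain, and the contrast used to size the trial is no longer between groups formed wholly by randomisation. Second, the protocol withholds primaquine from these patients at first treatment for safety, and then prescribes it for 21 days, mostly unobserved, if they recur.

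**Working it through.** **1. The plan's own figure.** Inputs from Sample size justification: 30% relapse on chloroquine, 4% on 14-day primaquine, 95% confidence (taken as two-sided 5%), 80% power, 20% loss.

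- Without continuity correction: n = [1.96·√(2·0.17·0.83) + 0.8416·√(0.30·0.70 + 0.04·0.96)]² / 0.26² = 31.6, so 32 per arm.
- With continuity correction: n = (31.56/4)·[1 + √(1 + 4/(31.56·0.26))]² = 38.9, so 39 per arm.
- Allowing for loss: 39/0.80 = 48.75, so 49 per arm, against 50 stated.

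The stated size reproduces and is not in dispute. The calculation does show that the sample size rests on chloroquine versus 14-day primaquine, the contrast that non-random entry would touch.

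**2. The statements side by side.**

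| Text followed | Deficient patient enters? | Arm |
|---|---|---|
| First words of the Trial Design bullet, with the randomisation rule | No | none |
| Second part of the same bullet | Yes | chloroquine alone, not by randomisation |
| Synopsis | Yes, unless severe | any of the three |

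The first two rows come from a single bullet. If every deficient patient were excluded, a clause barring them from two of three arms would have nothing to do. If they may enter the third arm, G6PD deficiency is not an exclusion, and the randomisation section lacks the route they would need.

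**3. Size if deficient patients are placed directly on chloroquine.** The protocol gives no prevalence of deficiency, so p = 1–10% is an assumption. The total is held at 150 and the remaining patients are split equally.

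| p | Deficient, 150p | Each primaquine arm, (150 − 150p)/3 | Chloroquine arm | Deficient share of chloroquine arm | Meet recurrence rule, 150p × 0.30 |
|---|---|---|---|---|---|
| 1% | 1.5 | 49.5 | 51 | 2.9% | 0.45 |
| 5% | 7.5 | 47.5 | 55 | 13.6% | 2.25 |
| 10% | 15 | 45 | 60 | 25% | 4.5 |

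The last column uses the protocol's 30% relapse rate, before loss to follow-up. With the protocol's 20% loss it becomes 0.36–3.6. Under strict exclusion every deficient count is 0.

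**4. Dose under the recurrence rule.** 21 × 0.25 = 5.25 mg/kg in total, against 14 × 0.25 = 3.5 mg/kg in the 14-day arm. The daily dose is the same; only the duration differs. No risk ratio follows from this.

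**5. Screening cost of strict exclusion.** 150/0.99 = 151.5, about 2 more patients screened; 150/0.90 = 166.7, about 17 more.

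**The case against.** The strongest reply is that both halves of the Trial Design bullet agree on what matters most: a patient deficient on the spot test does not receive primaquine at first treatment. With the randomisation rule and the exclusion for known contraindications, a site could reasonably conclude that no deficient patient enters. At recurrence, the Additional visits section has patients treated according to clinical need, and Ethics speaks of rescue treatment in similar terms, so no physician is compelled to give primaquine.

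Much of this stands, and it limits the point. It does not remove the contradiction. The clause implying chloroquine-only entry is itself in the body of the protocol, so setting the Synopsis aside does not settle the matter. The contraindication bullet does not say what degree of deficiency contraindicates primaquine. The discretion wording permits withholding primaquine but never says to withhold it.

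Some stronger readings are tempting but not supported:

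- **Deficient patients will be randomised to primaquine.** A reader might infer this from the Synopsis. It requires a site to follow a one-line summary over the explicit bar in the full criteria, so no headline probability should be built on it.
- **The spot-test result may come after allocation.** The test appears again among the admission samples ("On study admission, immediately before drug administration, blood will be collected for the following"), but it is already listed under screening, and the randomisation rule requires exclusions to be settled first.
- **The recurrence rule also fails women who become pregnant or breast-feed during follow-up.** Both are entry exclusions ("For females: pregnancy, breast feeding"), but the protocol states no specific hazard for them. The point is separate from the G6PD contradiction and is not pursued here.

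**Conclusion.** The concern holds as an inconsistency in a safety criterion, with a conditional consequence. The protocol does not fix whether deficient patients are excluded, enter on chloroquine alone, or are excluded only if severe.

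If they enter on chloroquine alone, the chloroquine versus 14-day comparison is not fully randomised. About 1.5–15 of 150 patients would be placed in the chloroquine arm by test result, and about 0.45–4.5 of them would meet an unqualified 21-day primaquine rule before loss to follow-up. These figures rest on the assumed 1–10% prevalence, on direct placement of every deficient patient, and on the protocol's 30% relapse rate applying to them. Under strict exclusion the figures are 0.

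A reader might infer that the primary result is compromised or that the chloroquine comparison is biased in a known direction. Neither follows. Allocation between the 5-day and 14-day arms stays random when deficient patients go only to chloroquine. Nothing in the protocol says that G6PD status alters relapse risk, so the direction and size of any bias are unknown.

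**What to change.** Adopt one rule: a patient deficient on the screening spot test is not randomised.

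1. Synopsis, Exclusion Criteria: replace the entry on severe deficiency with G6PD deficiency on the spot test.
2. Trial Design, Exclusion Criteria: delete the clause about the two primaquine groups. The randomisation section then agrees as it stands. If the investigators want to follow deficient patients on chloroquine alone, say so and keep them outside the randomised comparison.
3. Study drug regimens, recurrences: add that primaquine is not given to any patient deficient on the spot test. Under strict exclusion this covers patients enrolled in error; it is essential if deficient patients are followed outside the randomised arms.

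The cost is wording in three places, an ethics amendment where required, and slightly fewer eligible patients: about 2–17 more to screen at the assumed prevalence. No new test is needed and the sample size does not change.

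### The G6PD exclusion is stated in two incompatible ways, and the 21-day primaquine regimen for recurrences carries no G6PD condition

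*Protocol*

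**What the plan says.** The Protocol states the G6PD criterion twice.

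- Synopsis, Exclusion Criteria: "Severe G6PD deficiency". No grade or cut-off is attached.
- TRIAL DESIGN, Exclusion Criteria: "G6PD deficiency;patients who are deficient on spot testing will not be allocated to the two primaquine groups". The first two words name deficiency of any grade. The rest bars spot-test-deficient patients from two of the three arms.

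The only G6PD investigation in the document is the "G6PD spot test". It is listed among the screening tests and again among the samples taken on admission, just before dosing.

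Under Randomisation and blinding, patients who meet the inclusion criteria and "have none of the exclusion criteria will be randomised 1:1;1 to one of the three treatment arms", by drawing the next numbered envelope. That section says nothing specific about G6PD.

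For recurrences, Study drug regimens gives a single regimen: "chloroquine (25mg base /kg total) followed by primaquine 0.25mg base/kg daily for 21 days". It is not conditional on G6PD status, and the Concomitant Medication section refers back to it. On supervision: "The first dose will be observed but all subsequent antimalarial doses will be taken at home".

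**The concern.** The two lists admit different populations, and nothing says which prevails. The Background itself says that drugs of primaquine's class all cause oxidant haemolysis and warns of danger where G6PD deficiency is common. Eligibility is therefore the main protection for deficient patients, and it is the part of the document that conflicts with itself.

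The second half of the TRIAL DESIGN bullet adds a further uncertainty. If deficient patients are excluded outright, they are allocated to no arm, and a bar on only two arms is redundant. A site could take it to mean that they may enter on chloroquine alone. Such a patient would avoid primaquine at entry and then, at a recurrence, fall under the longest primaquine course in the trial. The patient would also have joined the chloroquine arm outside the 1:1:1 envelope sequence.

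**Working it through.** The plan gives no figure on this point, so the check sets the texts side by side and follows a deficient patient through each reading.

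**Inputs.** Entry regimens: chloroquine alone, or with 5 or 14 daily doses of primaquine (Study drug regimens). Recurrence regimen: 21 daily doses (same section). Allocation: 1:1:1 (Randomisation and blinding). Observed: the first dose only (Study drug regimens; Compliance with Study Drugs).

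| Reading | At entry | If malaria recurs |
|---|---|---|
| TRIAL DESIGN bullet as full exclusion | not enrolled, 0 primaquine doses | not in the trial, 0 doses |
| Synopsis, severe deficiency | excluded, 0 doses | not in the trial, 0 doses |
| Synopsis, non-severe deficiency | randomised: 0, 5 or 14 doses, with primaquine in 2 of 3 arms | 21 doses, whichever arm |
| TRIAL DESIGN clause as entry on chloroquine alone | 0 doses | 21 doses |

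**Doses taken at home.** With one dose observed, at least 5 − 1 = 4, 14 − 1 = 13 and 21 − 1 = 20 primaquine doses are at home. Each regimen starts with chloroquine, so if the observed dose is chloroquine, all 5, 14 or 21 are at home. The Summary of Trial Design describes both entry regimens in that way: "CQ plus 5 days unobserved primaquine or CQ plus 14 days unobserved primaquine".

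**Can the synopsis criterion be applied?** Not as written. It needs a grade of deficiency. The only test is a spot test, for which the document gives no grade or cut-off.

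**Is there a route to chloroquine alone?** The randomisation text offers none: it covers only patients with no exclusion criterion and spreads them over all three arms. This counts against that reading of the clause. It also means that a site adopting it would be working outside the described procedure.

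**What would detect harm?** Haematocrit is listed at screening or admission, at a recurrence and at premature discontinuation. None is scheduled during a primaquine course. Clinical contact does exist: visits are daily until fever resolves and then weekly for a month, symptomatic patients are assessed at unscheduled visits, and an adverse event can lead to withdrawal with follow-up until it resolves or stabilises. The document does not say that the early visit schedule restarts after a recurrence, when the 21-day course would be taken.

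**How often would the recurrence regimen apply?** The number of deficient patients is not derivable, because no prevalence is stated. The sample size section assumes 30% relapse on chloroquine alone. If a deficient patient placed on chloroquine alone relapsed at that rate, about 3 in 10 such patients would be assigned the 21-day course. This borrows the planning rate for the whole arm and is not a figure for deficient patients.

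**The case against.** The strongest reply is that the body of the Protocol governs and is protective. On either reading of the TRIAL DESIGN bullet, a spot-test-deficient patient receives no primaquine at entry. The bullet sits under an exclusion heading, and randomisation requires that no exclusion criterion be met. Both lists, including the synopsis, also exclude a known contraindication to the drugs, which could cover a patient found deficient. With only one ungraded test, a site might simply treat any deficient result as what the synopsis means by severe.

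Much of this stands. It makes full exclusion the likelier intent and rules out several stronger inferences:

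- A reader might infer that the body text itself directs primaquine to deficient patients at entry. It does not. Exposure at entry requires a site to work from the synopsis.
- A reader might take the word *applicable* in "All study patients must meet the applicable inclusion and exclusion criteria" as a sign that deficient patients are only partly excluded. That is strained. The same list has a criterion that applies to females only, which explains the word.
- A reader might conclude that nothing would catch haemolysis. The visits and withdrawal provisions set out above contradict that. What can be said is that no haematocrit is scheduled during a course.

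The reply does not remove the conflict. The contraindication bullets do not name G6PD, the document does not equate a deficient spot test with severe deficiency, and no text conditions the recurrence regimen on G6PD status.

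**Conclusion.** The point holds as a contradiction in an eligibility rule that bears on safety. Following the synopsis, a patient with non-severe deficiency could be randomised, with primaquine in two of three arms, for 5 or 14 days. Following the synopsis, or reading the TRIAL DESIGN clause as entry on chloroquine alone, a deficient patient whose malaria recurs would be assigned 21 days of primaquine, with at least 20 doses at home. Following the TRIAL DESIGN bullet as a plain exclusion, there is no exposure.

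These are doses per patient under each reading. The 5- and 14-day figures apply to non-severe deficiency only, and the 21-day figure only to patients who recur. How many patients would be exposed cannot be said, and no effect on the endpoint or the 50 per arm has been shown. Correction is still needed, because the text decides who may receive a drug whose hazard the Protocol itself describes.

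**What to change.** Use one criterion in the synopsis and in TRIAL DESIGN: G6PD deficiency on the screening spot test. In the synopsis, delete the word severe and add the test. In TRIAL DESIGN, delete everything after the semicolon and add the test. State that the result must be known before the envelope is drawn, since the test is also listed with the samples taken just before dosing. The randomisation text and the recurrence regimen can then stay as they are, because no patient deficient on the test would be in the trial.

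If entry on chloroquine alone is truly intended, say so. Define these patients as a separate non-randomised group outside the 1:1:1 comparison and outside the 150, state that they do not receive the 21-day primaquine regimen at a recurrence, and have the clinical team name what they receive instead.

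The cost of the preferred change is wording, as the test is already planned. A few more patients may need to be screened if deficient patients would otherwise have been enrolled, and none if full exclusion already applies. The alternative costs extra patients beyond the 50 per arm and a further recurrence treatment.
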